### Procedures, recruitment, randomisation, collection of baseline data

This trial will be a multicentre, open-label, randomised controlled trial. The study will be performed within the Dutch Consortium for Studies in Women’s Health and Reproductivity (http://www.studies-obsgyn.nl). Participating hospitals can be district, teaching or academic hospitals. Before entry into the study, women will be informed about the aims, methods, reasonably anticipated benefits and potential hazards of the study. This will generally be at least 1 day before actual admission for induction. They will be informed that their participation is voluntary and that they may withdraw consent for participation at any time during the study. Choosing not to participate will not affect care. In each centre an independent physician will be available for more detailed information for both patients and colleagues if desired. After counselling, written informed consent will be obtained. The consent form must be signed before performing of any study-related activity. Randomisation will be performed web-based using ALEA. After entering patient initials, confirming inclusion criteria and absence of exclusion criteria, randomisation will be performed realtime based on an algorithm. We will use fixed block sizes of 2 and 4 and stratify for centre and parity. As there is no prespecified randomisation list, it will be hardly possible for anyone to know the next allocation. Randomisation will take place after evaluation of the fetal condition by CTG, just before start of induction. Eligible women will be allocated in a 1:1 ratio to induction with a Foley catheter or oral misoprostol. There will be no blinding of patients and caregivers, as this is not feasible with these two treatment methods. Baseline demographic, obstetric and medical histories, and details of delivery and health care received till the time of discharge will be recorded for all women. Data will be entered into an electronic case-record form (Oracle Clinicle version 4.5.3) accessible through our study website with a personal login http://www.studies-obsgyn.nl/probaat2. All changes made in this electronic case-record form will be captured in an audit trial. In Oracle Clinicle checks will be programmed to identify errors. All electronic case-record forms will be checked for consistency and to correct errors.

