### Analysis

This trial is designed as a non-inferiority trial. Primary analysis will be by intention-to-treat. In a comparative trial, where the aim is to decide if two treatments will be different, an intention-to-treat analysis is generally conservative: the inclusion of protocol violators and withdrawals will usually make the results from the two treatment groups more similar. However, for a non inferiority trial this effect is no longer conservative: any blurring of the difference between the treatment groups will increase the chance of declaring non inferiority [17]. We will therefore also perform a per protocol analysis. Relative risks and 95% confidence intervals will be calculated for the relevant outcome measures. We will additionally adjust for the stratified randomization when calculating the relative risk. Differences between categorical variables will be tested with the Chi-square test, or if the expected cell count is below 5 with the Fisher’s exact test. Non-normally distributed continuous variables will be tested with the Mann–Whitney *U* test. Time to delivery will be assessed using Kaplan-Meier analysis. For the economic analysis we plan a cost-minimisation procedure, as we designed a non-inferior trial and expect no differences in outcomes. Resource uses are multiplied by their specific costs, which are estimated according to recent guidelines on costing health care services. When a relevant differences in outcomes will be observed, we will perform a cost-effectiveness analysis, in which we calculate the additional cost per prevented case of fluxus or asphyxia and the cost per prevented Caesarean section. Mean resource use and costs are compared between both arms, if any difference of interest in primary and/or secondary outcomes occurs a cost-effectiveness analysis will be performed. Using an interaction term we will assess whether the difference in effect between misoprostol and Foley catheter is consisted in nulliparous and multiparous women.

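### Randomisation is stratified by centre and parity, but stratum adjustment is only an addition on the relative-risk scale, away from the absolute 5-point margin, and no deciding estimate is named

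*Protocol article*

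**What the plan says.** **Design** (Protocol article, Procedures, recruitment, randomisation, collection of baseline data): "We will use fixed block sizes of 2 and 4 and stratify for centre and parity". Allocation is 1:1.

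**Analysis** (Protocol article, Analysis):
- Effect estimates: "Relative risks and 95% confidence intervals will be calculated for the relevant outcome measures".
- Strata: "We will additionally adjust for the stratified randomization when calculating the relative risk".
- Categorical outcomes: "Differences between categorical variables will be tested with the Chi-square test, or if the expected cell count is below 5 with the Fisher’s exact test".
- Skewed outcomes: "Non-normally distributed continuous variables will be tested with the Mann–Whitney" U test.
- Time to delivery: "Time to delivery will be assessed using Kaplan-Meier analysis". No comparison test and no strata are named.
- Parity also appears in a treatment-by-parity interaction term, which checks whether the effect is consistent.

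**Margin** (Protocol article, Sample size): non-inferiority means an absolute difference below 5 points in the composite, with 930 women per group, 80% power and one-sided 0.05. The same margin is applied to caesarean section, at 23% in both groups and with more than 80% power. The calculation is a two-group method without strata.

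**The concern.** Blocks of 2 and 4 within centre-by-parity strata hold the arms nearly balanced on both factors. Between-stratum variation then no longer contributes to the treatment contrast, but a crude standard error still counts it. If parity or centre predicts the outcome, crude intervals are somewhat too wide and crude tests somewhat conservative.

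There is also a question of scale and order. The non-inferiority conclusion is defined on the absolute difference. The Analysis section names no risk difference, crude or adjusted, and promises adjustment for the relative risk only. A relative risk does not translate into a fixed absolute margin. With a reference risk of 12.7%, 5 points corresponds to 17.7/12.7 = 1.39. At illustrative reference risks of 10% and 15% it corresponds to 15/10 = 1.50 and 20/15 = 1.33. So the adjusted result cannot be read directly against the margin, and where crude and adjusted results differ the article gives no order of precedence.

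**Working it through.** **1. The plan's own figure.** Inputs from Sample size: 12.7% and 13.7%, margin 5 points, hence 4 points to the margin; one-sided 0.05; 80% power.
- n per arm = (0.127×0.873 + 0.137×0.863)(1.645 + 0.842)²/0.04² = 886.
- Allowing for 5% exclusion: 886/0.95 = 933 per arm (1866 in total), or 886×1.05 = 931 (1862).

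The stated 1860 is reproduced by an unstratified formula. For caesarean section, power = Φ(0.05/SE − 1.645) with SE = √(2×0.23×0.77/n). This gives 82.0% at 930 per arm and 80.3% at 884 (930×0.95). Both stated powers hold without stratifying.

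**2. Formulas for the gain.** Let f be the nulliparous share, pₙ and pₘ the risks in nulliparous and multiparous women, and p the overall risk.
- Share of variance explained by parity: v = f(1−f)(pₙ−pₘ)²/[p(1−p)].
- Stratified SE = crude SE × √(1−v). The crude interval is too wide by 1/√(1−v) − 1.
- Stratified power = Φ(d/SE_strat − 1.645), where d is the distance to the margin.
- Crude power under stratified allocation = Φ(d/SE_strat − 1.645/√(1−v)). The estimate is already as precise; only its reported SE is too large.
- True one-sided error of the crude test = 1 − Φ(1.645/√(1−v)).

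The documents give no stratum rates, so every f, pₙ and pₘ below is an assumption.

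**3. Composite** (p = 13.2%, 884 per arm, d = 4 points, crude SE 0.0161, planning-formula power 79.9%):

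| f | risk ratio | v | crude interval too wide | crude power | stratified power |
|---|---|---|---|---|---|
| 65% | 1.5 | 0.5% | 0.3% | 80.0% | 80.1% |
| 65% | 2 | 1.3% | 0.6% | 80.1% | 80.4% |
| 65% | 4 | 3.6% | 1.8% | 80.4% | 81.2% |
| 50% | 4 | 5.5% | 2.9% | 80.6% | 81.9% |

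Against the planning figure of 79.9%, the gain runs from 0 (strata not prognostic) to 2 points. Against the crude test's actual power it is at most about 1.3 points. Adding an assumed between-centre SD in risk of 3 to 4 points to parity at 65% (risk ratio 2 to 4) gives stratified power of 80.7 to 81.7%. True one-sided error of the crude test is about 4.5 to 5.0%.

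**4. Caesarean section** (p = 23%, 930 per arm, d = 5 points, crude SE 0.0195):

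| f; pₙ v pₘ | v | crude interval too wide | crude power | stratified power |
|---|---|---|---|---|
| 65%; 30% v 10% | 5.1% | 2.7% | 82.7% | 83.8% |
| 60%; 32% v 9.5% | 6.9% | 3.6% | 82.9% | 84.4% |
| 50%; 36% v 10% | 9.5% | 5.1% | 83.3% | 85.3% |

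The gain is about 1 to 2 points. A simulation of 40,000 trials stratified by parity agrees: 82.7% v 83.8% in the first row and 83.1% v 85.2% in the last.

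**5. How often the verdicts part.** With balanced strata the crude and stratified risk differences nearly coincide and only the interval width differs. In that simulation the verdicts differed in about 1.1 to 2.0% of trials for caesarean section, and in about 0.3% for the composite at 16% v 8%.

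**The case against.** Adjustment for the strata is promised, and the word that introduces it can mean a further step in the main calculation as easily as a second estimate. The sample size never relied on adjustment. A slightly conservative test cannot manufacture a non-inferiority claim. The choice of stratified tests, and the handling of small centres, is detail that a condensed article may leave to an analysis plan. All of this stands, and it limits the point to what the article itself fixes: the methods it names, the scale it chose for adjustment, and the scale of the margin.

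A reader might infer more than the documents support:
- **That the strata are ignored.** They are not. An adjusted relative risk and a parity interaction are both planned. The interaction, though, is not a stratified comparison of treatments.
- **That planned power is lost.** The stated powers are reproduced and met by crude analysis; stratifying would be an addition to them.
- **That the gain on caesarean section is the gap between 82.0% and 83.8%.** The crude test's actual power under stratified allocation is about 82.7%, so the gain in that case is nearer 1 point.
- **That power on time to delivery is measurably reduced.** The article names no test and no power for it, so any figure would rest on an assumed log-rank test and assumed hazard ratios.
- **That the verdict could readily be picked.** Disagreement would be rare, and the planned adjusted relative risk is not on the margin's scale.

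**Conclusion.** The point holds as a modest matter of efficiency and clarity. The named tests do not follow the stratified design, the only adjustment promised is on a different scale from the margin, and the deciding estimate is not named. Nothing is lost against the stated power, and type I error is not inflated. The forgone gain is about 0 to 2 power points on the composite (about 0.3 to 0.5 at a parity risk ratio of 2 with 65% nulliparous, depending on the comparator) and about 1 to 2 on caesarean section, with crude caesarean intervals about 3 to 5% too wide. These sizes depend on assumed parity and centre risks and on the stated one-sided 0.05 level. If the strata do not predict the outcome, the gain is zero. The mismatch of scales and the missing order of precedence are read directly from the text and need no assumption.

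**What to change.** In the Analysis section, before data are seen:
- Name as the deciding analysis, for the composite and for caesarean section, a stratum-adjusted risk difference with its interval, for example Mantel-Haenszel over parity and centre, compared with the 5-point margin. Say how small centres are pooled.
- Keep the crude estimate and the adjusted relative risk as supportive.
- Compare the other outcomes with tests stratified at least by parity: Cochran-Mantel-Haenszel for binary outcomes, van Elteren for skewed ones, and a stratified log-rank or Cox comparison for time to delivery.

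The cost is analysis wording only. Both factors are known at randomisation, so no women, data or procedures are added, and the sample size can stay as it is.

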
## Methods/Design

### Aims

The aim of this study is to assess the safety and cost-effectiveness of induction of labour with a transcervical Foley catheter as compared to induction with oral misoprostol in term pregnant women with an unfavourable cervix.

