### Sample size

To calculate an adequate sample size we searched the literature for comparisons between oral misoprostol and Foley catheter. There is only one study which directly compared induction of labour with oral misoprostol and Foley catheter. This study does not report on our primary outcome measures which makes it insufficient to use for our power calculation [10]. A few studies reported on a comparison of vaginal misoprostol and prostaglandin E2, but different dosages were used and from the reported outcome parameters it was not possible to calculate the composite outcome we use [6]. Therefore we used data from the PROBAAT trial, comparing prostaglandin E2 (prostin) with Foley catheter [9]. In the Probaat trial the incidence of the composite outcome of pH ≤ 7.05 and/or an Apgar < 7 at 5 minutes (at least one known) and/or haemorrhage ≥1000 cc post partum was 12.7% when a Foley catheter was used and 16.4% when Prostaglandin E2 gel was used. We expect the incidence of the composite outcome to be lower when using oral misoprostol than when using prostaglandin E2 but slightly higher than when a Foley catheter is used [5]. We expect that about 25% of umbilical cord pH’s will be missing, while the 5 minute Apgar will be complete in nearly all cases. So, if the umbilical artery pH data will be missing, neonatal outcome will be classified as abnormal if the 5 minute Apgar will be <7 and as normal if the Apgar was ≥ 7. With a power of 80% (1-β) and a one-sided 0.05 risk of type I error (α), we need 1860 participants (930 per group) to demonstrate non-inferiority, i.e. that the absolute difference in the composite outcome will be less than 5% in the misoprostol group compared to the Foley catheter group, when assuming that the composite outcome was 12.7% in the Foley catheter group and 13.7% in the misoprostol group and an 5% exclusion rate from the per protocol analysis. This sample size will also give us more than 80% power to demonstrate non-inferiority, i.e. less than 5% increase in the proportion of caesarean sections when using misoprostol compared to Foley catheter, assuming 23% caesarean sections in both groups [9]. We used NQuery Advisor 7.0, with the two group test of equivalence in proportion (NQueryAdvisor; Machin 1987) to calculate the sample size.

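### Cost-minimisation is the default economic analysis because of the non-inferiority design, which does not show equal effects; the cost-effectiveness analysis should not wait for an observed difference

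*Protocol article*

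**What the plan says.** The Aims section of the protocol article sets the task without condition: "to assess the safety and cost-effectiveness of induction of labour" with the two methods.

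The Analysis section then fixes the economic method: "For the economic analysis we plan a cost-minimisation procedure, as we designed a non-inferior trial and expect no differences in outcomes". It departs from this in one case: "When a relevant differences in outcomes will be observed, we will perform a cost-effectiveness analysis". That analysis would report "the additional cost per prevented case of fluxus or asphyxia and the cost per prevented Caesarean section". Further on, the same section says that mean resource use and costs are compared between the arms, and that "if any difference of interest in primary and/or secondary outcomes occurs a cost-effectiveness analysis will be performed".

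The Sample size section does not assume equal outcomes. It expects the composite of asphyxia or haemorrhage with misoprostol to be lower than with prostaglandin E2 gel "but slightly higher than when a Foley catheter is used". It works with 12.7% for Foley and 13.7% for misoprostol, a margin of 5 percentage points, one-sided alpha of 0.05, 80% power and 930 women per group.

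**The concern.** Cost-minimisation compares costs alone. It is sound when the effects are known to be equal, because it sets both the effect difference and its uncertainty to zero. The plan gives two reasons for that step, the non-inferiority design and the expectation of no differences. The first does not establish equality, and the second conflicts with the trial's own sample size assumption.

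The way out of the default is an observed difference, so the choice of economic method is made from the results. If the observed difference is judged not relevant, no cost per prevented event is produced, although cost-effectiveness is half of the stated aim. What is at stake is whether the trial gives a formal answer to its economic question, and whether that answer carries the uncertainty in the clinical effects.

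**Working it through.** **Inputs** (all from the Sample size section): Foley 12.7%; misoprostol 13.7%; margin 0.05; one-sided alpha 0.05 (z = 1.645); power 80% (z = 0.842); 930 per arm; 5% excluded from the per protocol analysis.

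**1. The plan's own figure.** With unpooled variance,

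n = [0.127×0.873 + 0.137×0.863] × (1.645 + 0.842)² / (0.05 − 0.01)² = 886 per arm.

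886 / 0.95 = 933 per arm, or 1866 in total, against 1860 stated. The sample size reproduces and is not in dispute. It reproduces only with the 1-point difference working against the margin (distance 0.04). The trial was therefore sized on unequal outcomes.

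**2. How much a finding of no difference would show.** At the assumed rates,

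SE = √[(0.127×0.873 + 0.137×0.863)/930] = 0.0157.

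The 95% half-width is 1.96 × 0.0157 = 0.031, or 3.1 points. The power to find the assumed 1-point difference significant at two-sided 0.05 is about Φ(0.010/0.0157 − 1.96) = 9%. A non-significant difference is thus the likely result even if the plan's own assumption is true, and it would leave differences of about 3 points open.

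**3. How much the word relevant decides.** The chance that the observed composite difference reaches a given size in either direction, by the normal approximation with the same SE, is:

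| Observed difference at least | True difference 0 | True difference 1 point |
|---|---|---|
| 1 point | 52% | 60% |
| 2 points | 20% | 29% |
| 3 points | 6% | 11% |

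The reading of relevance moves the chance of a switch on this outcome from over half to about one in ten or less. The true difference matters much less.

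**4. An example.** Suppose 12.7% against 14.7% is observed with 930 per arm.

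SE = √[(0.127×0.873 + 0.147×0.853)/930] = 0.0159.

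The upper 90% limit is 0.020 + 1.645 × 0.0159 = 0.046, which is below 0.05, so non-inferiority is met in the direction used in the Sample size section. The difference is not significant: 0.020/0.0159 = 1.26, below 1.96. Yet it is twice the difference assumed in planning, and equals 20 cases per 1000 women (upper limit 46). One analyst could call this irrelevant and compare costs only. Another could call it relevant and run the cost-effectiveness analysis. The text supports both.

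**The case against.** The best defence has four parts.

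- **The rule is declared in advance, and details may sit elsewhere.** A threshold for relevance and the handling of uncertainty are commonly left to an analysis plan, and their absence from an article is no fault. This stands, so the point does not rest on the missing threshold. It rests on what the article states: a rationale that does not hold, and a method chosen from observed results. A threshold would cure neither.
- **Complications are not ignored in a cost comparison.** Resource use is collected across the phases of delivery, admissions and complications are recorded, and effects are reported with 95% confidence intervals. This stands too. A reader might infer that the cheaper method must win by construction, whatever its complications. The documents do not support that, because haemorrhage and asphyxia enter the costs to the extent that they use resources. What is lost is the health effect itself and the joint uncertainty.
- **The two statements of the switch are largely one rule worded twice.** A reader might see two conflicting triggers. The second wording mainly spells out that secondary outcomes count, so a contradiction is not established.
- **So broad a trigger makes a cost-effectiveness analysis likely.** Assume, for illustration, that a difference of interest means p < 0.05 on independent outcomes with no true effect. At least one would then arise with probability 1 − 0.95¹⁰ = 40% for 10 outcomes and 1 − 0.95²⁰ = 64% for 20. The real outcomes are correlated, so this is only indicative. It weakens any claim that the aim will go unanswered, but it confirms that chance results could choose the method.

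**Conclusion.** The point holds in a limited form. Neither the non-inferiority design nor the expectation of no differences justifies cost-minimisation as the default. A 5-point margin does not show equality, the plan itself assumes a 1-point difference, and the half-width of about 3.1 points at 930 per arm means that an unremarkable observed difference would not justify setting the effect and its uncertainty to zero. The method depends on the results, and the unconditional aim may not receive a formal estimate.

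A reader might infer from the 2-point example that declaring non-inferiority leads to cost-minimisation, so that 20 extra cases per 1000 would be ignored. The documents do not say so: the switch hangs on an observed difference, not on the non-inferiority verdict, and the example shows only that either course is open.

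The figures rest on the plan's assumed rates, 930 analysed per arm and the normal approximation. The example takes misoprostol as the arm tested against the margin, as the Sample size section does. The Abstract states the comparison the other way round, but that does not alter the argument. This is a secondary analysis; the primary conclusion, the sample size and the data collection are unaffected.

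**What to change.** In the Analysis section, make the cost-effectiveness analysis unconditional. Whatever the clinical result, estimate the cost difference and the effect differences (composite cases and caesarean sections, the two measures the plan already names) jointly with their uncertainty, for example by bootstrap. Report the comparison of mean costs as part of that analysis, and remove both conditional sentences and the appeal to the non-inferiority design. How the joint uncertainty is displayed is a matter of presentation and can be left to the analysis plan.

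If the effects prove equal, the analysis reduces in substance to a cost comparison, so nothing in the present plan is lost. The cost is a little extra analysis work on data already being collected, with no change to recruitment or the case-record form.

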### Sample size

To calculate an adequate sample size we searched the literature for comparisons between oral misoprostol and Foley catheter. There is only one study which directly compared induction of labour with oral misoprostol and Foley catheter. This study does not report on our primary outcome measures which makes it insufficient to use for our power calculation [10]. A few studies reported on a comparison of vaginal misoprostol and prostaglandin E2, but different dosages were used and from the reported outcome parameters it was not possible to calculate the composite outcome we use [6]. Therefore we used data from the PROBAAT trial, comparing prostaglandin E2 (prostin) with Foley catheter [9]. In the Probaat trial the incidence of the composite outcome of pH ≤ 7.05 and/or an Apgar < 7 at 5 minutes (at least one known) and/or haemorrhage ≥1000 cc post partum was 12.7% when a Foley catheter was used and 16.4% when Prostaglandin E2 gel was used. We expect the incidence of the composite outcome to be lower when using oral misoprostol than when using prostaglandin E2 but slightly higher than when a Foley catheter is used [5]. We expect that about 25% of umbilical cord pH’s will be missing, while the 5 minute Apgar will be complete in nearly all cases. So, if the umbilical artery pH data will be missing, neonatal outcome will be classified as abnormal if the 5 minute Apgar will be <7 and as normal if the Apgar was ≥ 7. With a power of 80% (1-β) and a one-sided 0.05 risk of type I error (α), we need 1860 participants (930 per group) to demonstrate non-inferiority, i.e. that the absolute difference in the composite outcome will be less than 5% in the misoprostol group compared to the Foley catheter group, when assuming that the composite outcome was 12.7% in the Foley catheter group and 13.7% in the misoprostol group and an 5% exclusion rate from the per protocol analysis. This sample size will also give us more than 80% power to demonstrate non-inferiority, i.e. less than 5% increase in the proportion of caesarean sections when using misoprostol compared to Foley catheter, assuming 23% caesarean sections in both groups [9]. We used NQuery Advisor 7.0, with the two group test of equivalence in proportion (NQueryAdvisor; Machin 1987) to calculate the sample size.

